## 10.1. Participant reimbursement

Participants will not receive any payments, reimbursement of expense or any other benefits or incentives for taking part in this research.

**10.2. Study Duration**

The study will last for 2 year, 11 months and 30 days in total (02/01/2017-31/12/2019). The study duration for each participant will be a maximum of 6 months (from initial drop-in to following up on impact of drop-in centre 6 months later).

**10.3. Definition of End of Study**

The end of study is the date of the last contact (i.e. 6 month follow-up) for the last participant.

1. **Statistical Considerations**

The number of people using the service and their feedback on it are the primary outcome measures for the feasibility study. This will include mean satisfaction ratings and written descriptions of the usefulness of the drop-in centre.

We will also look at the mean scores on the SDQ, PedsQL, PHQ-9 and GAD-7 in order to characterise the sample.

We will review medical records (with participants permission) over a six month period to categorise (a) the nature of the contact with the drop-in centre; (b) number of referrals to other services; and (c) number of hospital appointments over the six month follow-up period.

We will use t-tests and repeated measures analysis of variance to compare changes in mental and physical health over the six month follow-up period.

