| Clinical Intervention |  | The drop-in centre is funded as a research project and is currently not part of existing clinical services. If the project is successful and the centre is well-received, acceptable and effective then it will be incorporated into routine clinical practice. Therefore, we are viewing the intervention provided by the centre as research.  The intervention will vary depending on individual needs but is likely to include assessment, signposting to charities and support agencies and provision of evidence based low-intensity psychological interventions for common problems e.g. anxiety, sleep problems and behavioural difficulties.  The drop-in centre will be staffed by a qualified Psychological Wellbeing Practitioner, trained volunteers, a clinical psychologist and members of GOSH clinical teams (e.g. paediatric liaison) as appropriate. All staff will receive regular supervision from an experienced clinical psychologist, and will have access to the duty psychiatrist. |
| Measures |  | Mental health screening measures:   - Strengths and Difficulties Questionnaire (SDQ) - Patient Health Questionnaire (PHQ-9) - Generalised Anxiety Disorder Questionnaire (GAD-7) - Pediatric Quality of Life Inventory (Peds-QL)   Drop-in Centre Satisfaction Questionnaire  ONCE OFF – activity feed-back form |
| Follow up Measures |  | Mental health screening measures:   - Strengths and Difficulties Questionnaire (SDQ) - Patient Health Questionnaire (PHQ-9) - Generalised Anxiety Disorder Questionnaire (GAD-7) - Pediatric Quality of Life Inventory (Peds-QL)   Drop-in Centre Follow-Up Questionnaire (6 months after initial contact with centre). |
| End of Study |  | End of study is the last follow-up of the final participant. |

1. **Background**

Young people with physical illnesses are at significantly greater risk of developing emotional and behavioural problems than the general population. Such problems not only impact significantly on young people and their families, but can also have negative consequences for the management and course of the physical illness. Psychological treatments are highly effective for young people and adults but they are difficult to access. Parents and carers have also said that they find it difficult to access appropriate support for themselves when their child is physically unwell. There has been a recent drive to integrate physical and mental health care to improve access to evidence based psychological treatments.

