The overarching aim of this research is to establish the usefulness of a Psychological Wellbeing Drop-In Centre at Great Ormond Street Hospital (GOSH). We aim to deliver a friendly, accessible drop-in centre at the heart of public areas at GOSH where young people who are patients at the hospital and their carers can access advice about common emotional, behavioural and mental health problems. Families accessing the drop-in centre may receive a range of support from a team of trained mental health professionals including:

- Evidence based assessment of mental health difficulties
- Signposting to relevant services and third sector organisations
- Information and resources about common emotional and behavioural difficulties
- ‘Low intensity’ evidence based interventions for mild mental health problems e.g. anxieties, behavioural management and sleep problems.

The drop-in centre is not currently an existing service but if this project is successful and the centre is well-received, acceptable to patients and effective then it will be incorporated into routine clinical practice.

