**6. Specific Aims of the Study**

The aim of this study is to offer children and young people, and their families, quick and effective advice on their wellbeing and mental health needs. We are trying to improve the mental health and psychological wellbeing of any child attending participating sites who needs this support and ensure that any mental health needs are detected, diagnosed and treated.

The principal research question is: Do young people and their parents/carers find the drop-in centre for emotional/behavioural health at participating sites useful?

The secondary objectives are to evaluate the drop-in centre in terms of (i) the number of people accessing such a service, (ii) satisfaction, (iii) usefulness and, where possible, (iv) impact on health and (v) value for money.

1. **Study Design**

This is a feasibility study that is designed to assess user satisfaction and usefulness. All participants will receive the intervention from the drop-in centre in addition to treatment as usual.

Young people and parents/carers who approach the drop-in centre, or people in public areas of the hospital that are approached by the clinical research team and given a leaflet about the research, will be invited to participate. In addition, where interest is expressed and consent given, members of the patient’s direct clinical care team may sign-post or refer young people and parents/carers to the centre.

We will collect baseline data about young people and parent’s mental and physical health (SDQ, PHQ-9, GAD-7 and PedsQL measures) prior to their use of the drop-in centre in order to characterise the sample and identify the most common presentations.

The drop-in centre will provide evidence based information and support about common mental health difficulties. This will include assessment of needs, signposting to charities and support agencies, referral to other services and provision of low intensity psychological intervention. Low intensity means the most effective, but least intrusive, time consuming and expensive intervention. As the centre is funded as research, we are viewing these clinical interventions delivered by the drop-in centre as research.

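### Adoption is conditional on the centre being effective, but the planned before-after comparison has no control, cannot show this, and may well be significant with no effect

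*Protocol*

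**What the plan says.** The adoption condition appears twice. The Clinical Intervention row of the Study Synopsis says: "If the project is successful and the centre is well-received, acceptable and effective then it will be incorporated into routine clinical practice". The Background (Section 5) repeats it in nearly the same words: "if this project is successful and the centre is well-received, acceptable to patients and effective then it will be incorporated into routine clinical practice".

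Study Design (Section 7) describes a single arm: "All participants will receive the intervention from the drop-in centre in addition to treatment as usual". It also states the purpose: "This is a feasibility study that is designed to assess user satisfaction and usefulness". The aims in Section 6 place impact on health fourth of five secondary objectives, qualified as where possible. Section 10.2 describes the six-month contact as following up the centre's impact.

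Statistical Considerations (Section 11) sets the primary outcomes: "The number of people using the service and their feedback on it are the primary outcome measures for the feasibility study". It then names the one inferential analysis in the protocol: "We will use t-tests and repeated measures analysis of variance to compare changes in mental and physical health over the six month follow-up period". No comparator is named, and nothing in the protocol says what would count as effective.

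**The concern.** A within-person change from baseline to six months contains whatever the centre did, and also everything else that moves scores over six months. Four other sources of change can be read from the protocol itself:

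- **Regression to the mean.** Entry is partly need-driven. Families come forward themselves, or their clinical team refers those it expects to benefit (Section 9).
- **Usual care and natural course.** Everyone continues usual care, and the patients' underlying health may change.
- **Treatment elsewhere.** Those who screen as severe or at risk are referred to other services (Sections 10 and 13). Referral is partly a product of the centre, but the design cannot show what would have happened without it.
- **Selective follow-up.** Six-month contact depends on permission and on a reply, so responders may differ from non-responders.

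A test of change against zero cannot separate these from the centre's effect. At stake is a permanent service decision that names effectiveness as a requirement. A significant improvement could be taken to meet that requirement when it carries no such information.

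**Working it through.** **1. The plan's own figure.** The sample size section takes 1% of about half a million eligible people: 0.01 × 500,000 = 5,000, or 5,000/52 = 96 a week against the stated 100 or so. The figure reproduces. It is a projection of access, with no significance level, power, effect size or follow-up rate.

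**2. Pairs per test.** The 5,000 counts patients and carers together, and Section 10 splits each scale by respondent and age (for example, the child SDQ only from 11, the child PedsQL only from 8). If users came as patient-carer pairs there would be 2,500 families. With an assumed 50% follow-up, at most 1,250 pairs would remain per measure and respondent. Any one test will therefore have far fewer than 5,000 pairs.

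**3. Model with zero effect of the centre.** All inputs here are assumptions; the protocol gives none of them.

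- e = elevation of the users' baseline mean above the population mean, in SD units
- r = six-month correlation
- n = pairs with both measurements; two-sided 5% paired t-test
- Expected fall = e(1 − r)
- SD of change = √(2(1 − r))
- Standardised change d = e(1 − r)/√(2(1 − r))

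Example: e = 0.25, r = 0.7 gives a fall of 0.25 × 0.3 = 0.075 SD. The SD of change is √0.6 = 0.775, so d = 0.097. At n = 1,500 the expected t is 0.097 × √1,500 = 3.7.

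**4. Chance of p<0.05 with no effect** (noncentral t):

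| e | r | fall (SD) | n = 100 | n = 500 | n = 1,500 |
|---|---|---|---|---|---|
| 0 | any | 0 | 5% | 5% | 5% |
| 0.1 | 0.7 | 0.03 | 7% | 14% | 32% |
| 0.25 | 0.7 | 0.075 | 16% | 58% | 96% |
| 0.25 | 0.5 | 0.125 | 24% | 80% | >99% |
| 0.5 | 0.7 | 0.15 | 48% | 99% | >99% |
| 0.5 | 0.5 | 0.25 | 70% | >99% | >99% |

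Simulation agrees: 16% for e = 0.25, r = 0.7, n = 100; and for e = 0.5, r = 0.6, 59% at n = 100 and 100% at n = 1,500.

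**5. At the 1,250 pairs of step 2.** For e = 0.25, r = 0.7, a 90% chance of p<0.05 needs ((1.96 + 1.28)/0.0968)², about 1,120 pairs. So 1,250 pairs would still exceed 90%.

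**6. Smallest significant change.** 1.96/√n is 0.196 SD of the change score at 100 pairs, 0.088 at 500 and 0.051 at 1,500. Large numbers make small changes significant from whatever cause.

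Attribution fails at every n. Sample size governs only how often a spurious p<0.05 appears.

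**The case against.** The strongest reply is that the protocol already limits itself. It calls itself a feasibility study, its primary outcomes are use and feedback, and impact on health is secondary and hedged. This stands, and it lowers the severity. It does not remove the point: a study of that scope should not carry a condition it cannot assess, and the condition is joined to the others by *and*.

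A second reply is that no passage ties the adoption condition to a significant t-test, and that effectiveness might be defined in an analysis plan not shown here. The first part is correct. The second does not help, because no analysis plan can supply a comparator that the design lacks.

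A reader might be tempted to go further in three ways, none of which the protocol supports:

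- *The test is bound to be significant, so the condition cannot fail.* Elevation, correlation and pairs are all unknown. Leaflet recruits from public areas may be little elevated, and with no elevation the chance is 5%.
- *The before-after test is the only evidence.* Follow-up questionnaires are also collected, and records are used: "We will review medical records (with participants permission) over a six month period to categorise" contacts, referrals and appointments. These too have no control, but they exist.
- *Everyone enters in an acute hospital episode and is measured again at home.* Attendance within six months suffices, and the scales may be completed in the clinic, by telephone, by email or online. Home completion is stated only for the Follow-Up Questionnaire.

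It is also fair to say that a paired t-test and a confidence interval for the mean change carry the same information. The gain from the interval lies in showing the size of the change and in the label attached to it.

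**Conclusion.** The point holds in a limited form. Effectiveness is a stated condition for adoption, and the single-arm design cannot assess it. This conclusion follows from the protocol alone and needs no numerical assumption.

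That the test may well be significant without any effect is an illustration. It rests on an assumed elevation of 0.25 to 0.5 SD above the population mean, a correlation of 0.5 to 0.7, users as variable as the population, and a two-sided 5% level. In that range the chance is at least 96% with 1,500 or more pairs and 16% to 70% with 100. It falls to 5% with no elevation.

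Severity is should-fix. The adoption statement and a secondary objective are affected. Uptake, satisfaction and usefulness are not.

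**What to change.** - **Study Synopsis and Background (Section 5).** Remove effectiveness from the adoption condition, or add that this feasibility study does not assess it. Base adoption on usefulness, acceptability and uptake, which are the primary question and outcomes.
- **Section 11.** For each measure and respondent, report the mean change from baseline to six months with a 95% confidence interval and the number of pairs. Label this as descriptive. State that the change cannot be attributed to the centre, because there is no comparison group and entry is partly driven by need.

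The cost is wording; data collection does not change. The sponsor gives up an effectiveness claim that the design could not support. If that claim is wanted, it needs a comparison group, which this protocol does not provide.

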Following their use of the centre, participants will be asked to complete brief questionnaire/s to provide feedback on the service they received (Drop-In Centre Satisfaction Questionnaire and/or the ONCE OFF – activity feed-back form). They will also be asked for permission to contact them in six months to complete additional mental health measures (SDQ, PHQ-9, GAD-7 and PedsQL) and to further establish the usefulness of the Drop-In Centre in terms of further action (e.g., did they follow up on any of the information given), impact on physical health and use of physical or mental health services (Drop-In Centre Follow Up Questionnaire).

The number of people using the pod over the period of the project will be assessed.

1. **Participants**

All young people and parents/carers that either approach the Psychological Wellbeing Drop-In Centre or are approached by the clinical research team at GOSH will be potential participants.

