**10. Procedure**

Mental Health Measures

Following written consent, participants will be asked to complete up to three brief screening measures of mental health as follows:

**SDQ:** This is a brief screening questionnaire for common mental health problems in young people. It will be completed by parents only if the child is under 11 years, or by both the parent/carer and child if the child is aged 11 years or over. It will be completed in the drop-in centre

**PedsQL**: This is a brief assessment measure of young people’s quality of life. It will be completed by the parent/carer only if the child is under 8 years, or by both the parent/carer and child if the child is aged 8 years or over.

**PHQ-9:** This is a brief screening measure for depression in adults. It will be completed by parents/carers to assess parental mental health for children under 12. Children 12 years or over will complete this measure to assess child mental health.

**GAD-7:** This is a brief screening measure for anxiety in adults. It will be completed by parents/carers to assess parental mental health for children under 12. Children 12 years or over will complete this measure to assess child mental health..

The SDQ, PedsQL, PHQ-9 and GAD-7 are all routinely used in clinical practice.

Participants will complete these measures either in the clinic, over the telephone, via email or online in Redcap according to patient preference.

Planned Interventions

Families will have the opportunity to outline their concerns to a trained mental health professional. Depending on the nature of the difficulty, possible outcomes might be:

- Standardised assessment using web-based, evidence-based brief measures including opportunity to access a widely used standardised online detailed assessment of child mental health (Development and Wellbeing Assessment; DAWBA) and obtain an assessment report;
- Provision of information or self-help material/website suggestions;
- Signposting e.g. where to find appropriate support agencies, charities etc.;
- Referral to appropriate services either within Paediatric Psychology or Psychological Medicine at participating sites, Psychiatry at participating sties or in the local vicinity of the family; and/or
- Brief focussed evidence-based advice for common mental health problems e.g. behaviour management, childhood fears, sleep problems.

Care Pathways

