We will ask permission from all participants to contact them again in six months time to ask them for additional feedback on the centre. The Drop-In Centre Follow-Up Questionnaire will be sent by post or email according to participant preference six months after their first contact with the Centre. This will be completed by the parent/carer only if the child is under 11 years, or by parent/carer and child if child is over 11 years. It will be completed in participants own home and returned by post or email according to participant preference.

Medical records will be reviewed to characterise the nature of the intervention received from the drop-in centre, and number of appointments or referrals to other services during the six month follow-up period. Written consent will be sought prior to anyone outside of the direct clinical care team gaining access to participants' personal data.

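### The named tests for six-month change use only people with both scores, so the mean change can be biased if return depends on baseline severity

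*Protocol*

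**What the plan says.** Section 11 (Statistical Considerations) fixes the method for change in health: "We will use t-tests and repeated measures analysis of variance to compare changes in mental and physical health over the six month follow-up period". It names no between-person factor and does not say whether the t-tests are paired.

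The two time points come from Section 7 (Study Design). The SDQ, PHQ-9, GAD-7 and PedsQL are collected "prior to their use of the drop-in centre in order to characterise the sample and identify the most common presentations". For the second occasion, "They will also be asked for permission to contact them in six months to complete additional mental health measures". There is no comparison group: "All participants will receive the intervention from the drop-in centre in addition to treatment as usual".

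Section 10.1 says of incentives: "Participants will not receive any payments, reimbursement of expense or any other benefits or incentives for taking part in this research". No expected six-month return rate appears anywhere in the protocol.

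Section 11 makes uptake and feedback the primary outcomes. Impact on health is among the secondary objectives, to be evaluated where possible.

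**The concern.** Every participant is asked for baseline scores, but only those who give permission and then respond have six-month scores. A test of within-person change discards the rest, including baselines that may show how the non-responders differed.

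If the more severely affected return less often, the completers start below the full sample's mean on a scale where higher is worse. They then drift back towards that mean, and the analysis reads the drift as worsening. If the more severely affected return more often, the same drift looks like improvement. Either could mislead, because the protocol says the centre will enter routine practice if it is well received, acceptable and effective. The six-month change is the main quantitative evidence it will have on the last of these.

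**Working it through.** **Plan's own figure.** There is no power calculation to reproduce. The sample size of 5000 is an uptake projection: 1% × about 500,000 = 5000.

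**Are the two tests distinct?** With two times, one group and no other factor, the repeated-measures ANOVA statistic for time is F = t², where t is the paired t statistic. A numerical check on 200 simulated pairs gave 6.472 for both. ANOVA would add something only if a between-person factor were included, and none is named.

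**Inputs for the bias.** The protocol supplies none of these, so all are assumptions:
- scores standardised to mean 0 and SD 1 at both times, with higher meaning worse and true mean change 0;
- correlation between baseline and six months ρ = 0.6;
- log-odds of return falling 0.5 per SD of baseline;
- overall return of 70%, 50% or 30%.

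**Formula.** Let m be the responders' mean baseline. Their expected six-month mean is ρm, so the completers' mean change is ρm − m = −(1 − ρ)m = −0.4m.

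| Return | m | Completers' change (true value 0) |
|---|---|---|
| 70% | −0.143 | 0.4 × 0.143 = 0.06 SD |
| 50% | −0.236 | 0.4 × 0.236 = 0.09 SD |
| 30% | −0.333 | 0.4 × 0.333 = 0.13 SD |

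The values of m come from numerical integration of the return model over a standard normal baseline. With a weaker slope (odds of return × 0.67 per SD) the bias is 0.05, 0.08 and 0.11 SD. If return is unrelated to scores, m = 0 and the bias is 0.

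**What a likelihood model does with the same data.** It estimates the six-month mean as the responders' mean plus ρ × (mean baseline of all − mean baseline of responders). At 50% return the responders' six-month mean is 0.6 × (−0.236) = −0.142. The estimate is −0.142 + 0.6 × (0 + 0.236) = 0, so the estimated change is 0, which is correct.

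**An unpaired t-test is no escape.** Comparing all baselines (mean 0) with the returned six-month scores (mean −0.142) gives −0.14 SD at 50% return, and it ignores the pairing.

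**Would the bias be visible?** The SD of change is √(2 × (1 − 0.6)) = 0.894. At 50% return, t = 0.0944 / (0.894/√n), which is 1.7 with 250 pairs, 2.4 with 500, 3.3 with 1,000 and 5.3 with 2,500. The last needs half of the projected 5000 to form complete pairs on a single measure. Fewer are likely, since the 5000 mixes patients and carers and the scales differ by age and informant.

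**Limit of the remedy.** Suppose instead that return depends on the change itself, with odds × 0.67 per SD of change. At 70%, 50% and 30% return the completers' change is −0.10, −0.17 and −0.24 SD. The likelihood model still gives −0.08, −0.14 and −0.20 SD. It corrects only for loss explained by observed data.

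**The case against.** **Missing-data rules may sit in an analysis plan that is not shown.** That is fair, and the absence of such a rule is not the point here. The protocol does name the tests, and in standard form those tests need both scores.

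**The bias is conditional.** This stands. It is zero if return is unrelated to scores, and the mixed model leaves most of it if return depends on unobserved change.

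**A reader might infer that loss will be large.** The sentence "It will be completed in participants own home and returned by post or email according to participant preference" invites this, but it describes the Drop-In Centre Follow-Up Questionnaire, not the four scales tested for change. Section 10 allows the scales to be completed in clinic, by telephone, by email or online. Permission and lack of payment make some loss plausible; its size is unknown.

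**A reader might also infer that family members are treated as independent, so that intervals are too narrow.** The SDQ is completed "by both the parent/carer and child if the child is aged 11 years or over", and the PedsQL by both from age 8. With two pooled records per family, the design effect is 1 + (2 − 1) × ICC. An assumed ICC of 0.1 to 0.5 gives 1.1 to 1.5, so naive intervals would be 1/√1.1 = 95% to 1/√1.5 = 82% of the correct width. But the protocol does not say that informants are pooled. Analysed by informant with one record per family, the design effect is 1.0. For the PHQ-9 and GAD-7 the parent answers when the child is under 12 and the child answers from 12, so one child yields no parent-child pair. Siblings are never mentioned. Too-narrow intervals are therefore not established.

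**The stakes are low.** Largely true: uptake and feedback are primary, and this is a feasibility study.

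**Conclusion.** The point holds in a limited form. For two times and one group, the named tests amount to one test, and that test uses only people with both scores. It therefore leaves the completers' mean change open to bias that the baselines already held could reduce.

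Under the assumed inputs the bias is about 0.06 SD at 70% return and 0.13 SD at 30%, and zero if return is unrelated to scores. Correlation, return rate and selection strength are all assumptions. The redundancy of the two tests does no harm in itself. The documents support neither a claim that bias is certain nor a claim that intervals are too narrow.

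The change is worth making because a better method is available at little cost, but the point bears on a secondary objective only. A mixed model estimates the change in the enrolled sample better; it does not show that the centre caused it.

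**What to change.** Replace the sentence on t-tests and ANOVA in Section 11 with the following:
- A linear mixed (likelihood-based) model, fitted separately for each measure and each informant, with time as fixed effect and a person random effect. Include all available baseline and six-month scores, whether or not the pair is complete. Let the residual variance differ between the two times, so that the model does not force equal spread.
- Mean change with a 95% confidence interval for each measure and informant.
- A table of baseline scores for six-month responders and non-responders.
- A sensitivity analysis in which return depends on unobserved change, for example by shifting the non-responders' assumed six-month mean over a stated range.
- Family-cluster-robust standard errors, only where a family contributes more than one record to the same analysis.

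The cost is one paragraph in Section 11 and slightly more analysis work, plus a family identifier in the database if the last item applies. No extra data need be collected from participants.
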